## Abstract

Low-renin hypertension affects 1 in 4 people with hypertension, but the optimal management of this condition is not known. We hypothesize that a large proportion of people with low-renin hypertension is mediated by excess mineralocorticoid receptor (MR) activation and that targeted treatment with an MR antagonist (MRA) will be beneficial. This randomized, single-blinded, titration-to-effect aims to investigate whether targeted treatment in low-renin hypertension with MRA is better compared to standard antihypertensives in terms of blood pressure control and end-organ protection. Adults with hypertension, who are treatment naïve or are receiving up to two antihypertensive agents and have a low direct renin concentration <10 mU/L will be included. Participants with severe hypertension, a secondary cause of hypertension, pregnant, breastfeeding, with moderate-severe cardiovascular and chronic kidney disease, or on medications that confound interpretation of the plasma direct renin or aldosterone concentrations will be excluded. Eligible participants will be randomized 1:1 to either MRA therapy (spironolactone) or standard anti-hypertensive therapy (perindopril+/− amlodipine) for 48 weeks. Anti-hypertensives will be up-titrated every 12 weeks until target blood pressure is achieved. The primary objective will be to determine the total defined daily dose of antihypertensives required to achieve the target blood pressure and change in mean clinic systolic blood pressure at week 48. Current hypertension guidelines do not have specific recommendations for the choice of anti-hypertensive medications for people with low-renin hypertension. The results of this trial could guide future hypertension guidelines.

## Introduction

Hypertension is a major cause of death worldwide. Despite extensive research into optimal hypertension treatment, blood pressure control remains inadequate with 2 in 3 hypertensive patients not meeting blood pressure targets and often needing multiple anti-hypertensive medications to achieve control [1]. Missing a secondary cause of hypertension and the lack of a stratified approach for the treatment of hypertension have been highlighted as key shortcomings by the 2016 Lancet Commission on Hypertension [2].

Primary aldosteronism is now recognized as the most common cause of secondary hypertension, accounting for 10% of all people with hypertension [3]. Primary aldosteronism is characterized by autonomous aldosterone production in the presence of renin suppression. Under physiological conditions, the renin-angiotensin-aldosterone system plays a pivotal role in the maintenance of blood pressure through sodium and water homeostasis in epithelial tissues. However, in primary aldosteronism, aldosterone production is unregulated resulting in inappropriate activation of the mineralocorticoid receptor (MR) , which results in excess resorption of sodium and water, hypertension, and cardiovascular injury [4]. Diagnosis of primary aldosteronism provides an opportunity for effective treatment with either adrenalectomy or MR antagonists (MRA) such as spironolactone and eplerenone. Targeted treatment in primary aldosteronism with MRA improves blood pressure, and polypharmacy and reduces the elevated risk of cardiovascular disease in this population [5].

Importantly, primary aldosteronism is part of a renin-independent hyperaldosteronism continuum. Recent studies have reported the correlation between low renin, markers of increased MR activity, and progressive development of incident hypertension [6]. As such, people with a low direct renin concentration and various levels of aldosterone concentration that do not result in an aldosterone-to-renin ratio that meets the ‘positive’ screening threshold for primary aldosteronism are part of the continuum. Traditionally referred to as low-renin hypertension or low-renin essential hypertension, this condition may be present in up to 30% of people currently labelled as having essential hypertension [7, 8]. A recent meta-analysis comparing MRA to other antihypertensives has shown that MRA is more effective in lowering systolic blood pressure compared to commonly used first-line standard antihypertensives [9–11]. In addition, observational data suggests that MRA use in low-renin hypertension reduces end-organ dysfunction, for example, left ventricular hypertrophy and albuminuria [12]. Despite evidence supporting treatment that differs from standard practice, low-renin hypertension as a condition distinct from essential hypertension is overlooked due to renin and aldosterone concentrations being neither routinely requested nor used to guide initial therapy [10, 11]. The retrospective diagnosis of low-renin hypertension is challenging as many commonly used antihypertensives interfere with direct renin concentration interpretation [5]. At present, an add-on antihypertensive treatment strategy is recommended by guidelines, and MRA treatment is reserved as a fourth-line agent for resistant hypertension [10, 11]. We may therefore be missing an important opportunity to intervene early to provide targeted treatment with spironolactone, a widely used MRA that is readily available and inexpensive.

Personalizing treatment to the underlying pathophysiology for an individual is likely to improve blood pressure control with fewer medications and reduce/prevent end-organ damage [13]. However, translation to clinical practice has been limited due to concerns regarding the tolerability of MRA therapy and older clinical trials showing conflicting results likely due to suboptimal research methodology. Our study aims to address some of these limitations by conducting a single-blinded randomized controlled trial comparing targeted treatment with MRA versus commonly used standard antihypertensives in adults with low-renin hypertension [14]. We hypothesize that in a large proportion of patients with low-renin hypertension, the underlying pathophysiology involves MR activation and therefore targeted treatment with an MRA will offer greater antihypertensive effects and end-organ protection. This Randomized trial assessing the Efficacy and safety of Mineralocorticoid receptor Antagonist therapy compared to Standard antihypertensive Therapy in hypErtension with low Renin (REMASTER) therefore seeks to evaluate the efficacy and safety of MRA therapy in participants with low-renin hypertension and to evaluate the clinical, biochemical, and molecular markers that determine MRA responsiveness in people with low-renin hypertension.

## Methods and analysis

Reporting of the methods follows the SPIRIT guidelines [15].

### Trial design and study setting

The trial will be a randomized, single-blinded, active-controlled, titration-to-effect, pragmatic study comparing MRA to standard anti-hypertensive treatment for participants with low-renin hypertension referred to the Endocrine Hypertension Clinic at Monash Health, Victoria’s largest public health service. The clinic receives referrals from both general practitioners and specialists. Before performing any trial-specific procedures, a signed consent form will be obtained from each participant. The investigator will confirm that the participant comprehends the information provided and answer any questions about the trial. When the inclusion/exclusion criteria have been addressed and the eligibility of the participant confirmed, the participant will then be randomized 1:1 to one of the trial arms. All participants will undergo a seated saline suppression test to exclude primary aldosteronism. Renin concentration exists on a continuum. The definition of low-renin hypertension is somewhat arbitrary and has traditionally been defined as a plasma renin activity <1 ng/ml/h which approximately equates to a direct renin concentration of 8–12 mU/L. Furthermore, in an eight-week monotherapy study by Weinberger, participants with direct renin concentration <9.4 mU/L had a better blood pressure response to eplerenone compared to losartan: mean change in systolic blood pressure of –17.2 mmHg versus –5.4 mmHg [16]. We therefore selected a threshold of <10 mU/L to define low-renin hypertension.

### Trial population

#### Inclusion criteria

Adult ambulatory participants with hypertension, defined as a mean seated blood pressure >140/90 mmHg, and are treatment-naive or with any blood pressure level on up to two antihypertensive agents, have a low direct renin concentration <10 mU/L (measured on non-interfering medications), but who do not have primary aldosteronism or monogenic forms of low-renin hypertension, and can provide informed consent to participate in the trial.

#### Exclusion criteria

See Table 1.

**Table 1 Tab1:** Eligibility criteria.

Inclusion criteria	-Hypertension, defined as a mean seated blood pressure >140/90 mmHg and is treatment naïve or any blood pressure if receiving up to two antihypertensive agents. -Low direct renin concentration <10 mU/L (measured on non-interfering medications) -Can provide informed consent.
Exclusion criteria	-Blood pressure >180/120 mmHg. -On mineralocorticoid receptor antagonist treatment or medications confounding renin or aldosterone measurement e.g., glucocorticoids, oral estrogen, and sodium-glucose co-transporter 2 inhibitors. -Pregnant, breastfeeding or women of childbearing potential not on reliable contraception. -Hyperkalemic, potassium >5.0 mmol/L. -History of uncontrolled diabetes with glycosylated hemoglobin >7.5%, chronic kidney disease with an estimated glomerular filtration rate <50 mL/min/1.73 m^2^, heart failure class II–IV, ischemic heart disease, transient ischemic attack, stroke, or atrial fibrillation. -History of liquorice abuse or other secondary causes of hypertension such as primary hyperparathyroidism, primary aldosteronism, autonomous cortisol secretion, hyperthyroidism, phaeochromocytoma, renal artery stenosis or known monogenic causes of low-renin hypertension. -Known hypersensitivity to the trial medications.

### Trial procedure

Study participants meeting the inclusion and exclusion criteria will be randomized 1:1 via REDCap to either MRA, spironolactone (intervention), or standard care, perindopril+/-amlodipine (control), using a block randomization method. The schedule has been prepared by a biostatistician and uploaded to REDCap and is not available to the clinic staff. Participants on antihypertensive treatment at baseline will undergo a washout period of 2–4 weeks before screening and randomization. If there are clinical concerns, prazosin, a short-acting antihypertensive can be continued until 48 h pre-randomization. The standard care group will receive treatment as per local prescribing patterns and hypertension guidelines [14]. Antihypertensive medications will be titrated as required at 12-weekly intervals until target blood pressure of <140/90 mmHg is achieved in both groups and renin is unsuppressed i.e., >15 mU/L in the MRA group (Fig. 1). The biochemical titration target for the MRA group is based on evidence that treatment adequacy is associated with normalized renin [17]. Participants will be reviewed every 6–12 weeks and treated for a total of 48 weeks. Administration of medication will be standardized to night-time dosing once daily for consistency. Blood pressure measurements will be taken seated in triplicates using an automated blood pressure machine (Omron) and the average of 2nd and 3rd readings will be calculated. Automated office blood pressure measurement has been shown to correlate with out-of-clinic measures [18].

**Fig. 1 Fig1:**
[figure not shown]
Titration steps in the treatment algorithm.

Pathology will be collected at Monash Health Pathology laboratories. Both aldosterone and direct renin concentration will be measured using chemiluminescent immunoassays (LIAISON, DiaSorin). For the seated saline suppression test, aldosterone concentration will be measured using mass spectrometry as well due to its greater accuracy [19]. Primary aldosteronism will be excluded if aldosterone concentration post saline infusion is <162 pmol/L [20].

### Compliance

Medication compliance will be assessed at each study visit using medication diaries and pill counting when medications are returned to the pharmacy.

### Relevant concomitant therapies allowed and excluded

Women of childbearing age will need to be on effective contraception given the potential for teratogenicity of the trial medications during study participation and until 2 months after the last dose of trial medications. Trial participants needing to use medications that can interfere with the measurement of blood pressure, renin, or aldosterone during the treatment and follow-up phase of the trial will be excluded.

### Safety considerations

All medications used in the trial have been entered into the Australian Register of Therapeutic Goods. Spironolactone, perindopril, and amlodipine are approved by Therapeutic Guides Australia for the treatment of hypertension. The following adverse effects will be noted at each visit: gynecomastia, breast pain, reduced libido, menstrual irregularity, cough, hyperkalemia, and an increase of >30% in serum creatinine.

Adverse effects will be described in the patient’s medical record as follows: a description of symptoms including duration, severity (mild, moderate, or severe), seriousness (i.e., is it a serious adverse event?), any action taken, the outcome and likelihood of the relationship to the trial treatment (unrelated, possible, probable, definite) [21]. All serious adverse effects that occur from the time the participant signs the consent form, up to and including the last scheduled visit, will be reported within 24 h to an independent Data and Safety Monitoring Board, consisting of four members including a biostatistician and doctors with expertise in clinical trials. A trial progress update will be sent quarterly to the Data and Safety Monitoring Board. Trial conduct, protocol compliance, and safety are under their oversight.

### Dose and medication modification

If a participant on spironolactone treatment develops troublesome gynecomastia, breast tenderness, or irregular menses, they will be prescribed eplerenone in place of spironolactone at the same dose but twice a day e.g., participants on spironolactone 25 mg daily will be switched to eplerenone 25 mg twice a day. Eplerenone is a less potent but more selective MRA with minimal effect on the progesterone and androgen receptors. If perindopril 5/10 mg is not tolerated due to side effects such as cough, participants will be prescribed irbesartan 150/300 mg, respectively. Participants requiring a change in medication to eplerenone or irbesartan will be unblinded but will remain in the study and contribute to the final analysis. If a participant develops hyperkalemia, defined as serum potassium > 5.5 mmol/L on a non-hemolyzed blood sample, or has a 30% increase in creatinine due to perindopril/irbesartan or spironolactone/eplerenone, the dose of the trial mediation will be reduced to the highest tolerated dose.

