### Blinding

Participants will be blinded to the treatment by using encapsulating medications through a third party. The nurse and technician performing clinic blood pressure, and transthoracic echocardiograms will also be blinded to reduce any potential bias in the reporting of outcomes. Clinicians prescribing the antihypertensives will not be blinded to treatment allocation as the titration protocol is treatment-specific. Although a possible limitation, we anticipate that any treatment bias will be minimal given that the prescribed treatment will be driven by the study protocol and up-titration of treatments will be based on clinic blood pressure measurements performed by the nurse (blinded to treatment allocation), and direct renin concentration values measured at the hospital laboratory (for the MRA arm only).

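### A side-effect switch to eplerenone or irbesartan automatically unblinds the participant before the only post-treatment SF-36, and twice-daily eplerenone is inconsistent with the once-nightly dosing standard

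*Protocol article*

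**What the plan says.** All references are to the Protocol article.

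- **Blinding.** Participants: "Participants will be blinded to the treatment by using encapsulating medications through a third party". Assessors: "The nurse and technician performing clinic blood pressure, and transthoracic echocardiograms will also be blinded". Prescribers: "Clinicians prescribing the antihypertensives will not be blinded to treatment allocation as the titration protocol is treatment-specific". This section gives no exception for participants who change drug.
- **Dose and medication modification.** Breast symptoms or menstrual irregularity on spironolactone lead to a change of drug: "they will be prescribed eplerenone in place of spironolactone at the same dose but twice a day". In the control arm: "If perindopril 5/10 mg is not tolerated due to side effects such as cough, participants will be prescribed irbesartan 150/300 mg, respectively". For both: "Participants requiring a change in medication to eplerenone or irbesartan will be unblinded but will remain in the study and contribute to the final analysis".
- **Trial procedure.** "Administration of medication will be standardized to night-time dosing once daily for consistency". No exception is stated.
- **Tables 2 and 3.** SF-36 change to week 48 and discontinuation because of adverse effects are secondary objectives. SF-36 is scheduled at weeks 0 and 48 only, as are ambulatory BP monitoring (ABPM) and echocardiography. Clinic BP is also taken at the visits between. Adverse effects are recorded at weeks 6, 12, 24, 36 and 48.

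**The concern.** Because the prescriber knows the allocation from the start, the participant's own blinding is the main protection for what the participant reports. The plan withdraws it automatically at a switch and gives no reason why disclosure is needed.

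The participants who lose it are not a random subset. They are selected by side effects that differ between the drugs. SF-36 has a single post-treatment time point, so a switcher has no blinded value after baseline, and no later analysis can recover one. Symptom reports after the switch, and later decisions to stop, are also made with knowledge of treatment. The Introduction names worries about tolerability as one barrier to the use of mineralocorticoid receptor antagonists (MRAs), so these outcomes matter to how the trial will be read.

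The second issue is an inconsistency about dosing frequency. It bears on the conditions under which clinic systolic BP, a primary endpoint, and ABPM are measured in participants who move to eplerenone.

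**Working it through.** **1. The plan's own figures.** The plan gives no switch rate and no figure for the effect of unblinding, so there is none to reproduce on this point. The sample sizes (24 and 50 per arm) are not in dispute. A two-sample t-test at two-sided 0.025 and 90% power needs 20 and 41 evaluable per arm. Allowing for 20% attrition gives 24 to 25 and 50 to 52.

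**2. Which data are affected.**

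| Data | Before the switch | After the switch |
|---|---|---|
| SF-36 | Week 0, blinded | Week 48, unblinded |
| Complaint that triggers the switch | Reported while blinded | Not applicable |
| Later symptom reports | Not applicable | Unblinded |
| Clinic BP, ABPM, echocardiography | Participant blinded | Participant knows treatment; no text lifts the blinding of nurse or technician |
| Potassium, creatinine | Laboratory values | Laboratory values |

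**3. How many (assumed rates).** With 50 per arm, a 5% switch rate gives 50 × 0.05 = 2.5 participants and 20% gives 50 × 0.20 = 10.

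**4. Possible shift in the SF-36 difference (assumed inputs).** Let p1 and p2 be the switch rates in the two arms, and b the shift in a switcher's score caused by knowing the treatment, taken as 0.2 to 0.5 SD.

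- Same direction in both arms: shift = (p1 − p2) × b.
- Opposite directions: shift = (p1 + p2) × b.

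| Switch rates | Same direction | Opposite directions |
|---|---|---|
| 10% v 10% | 0 | 0.20 × 0.2 to 0.20 × 0.5 = 0.04 to 0.10 SD |
| 20% v 10% | 0.10 × 0.2 to 0.10 × 0.5 = 0.02 to 0.05 SD | 0.30 × 0.2 to 0.30 × 0.5 = 0.06 to 0.15 SD |

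For scale, the standard error of a standardised difference with 50 per arm is √(2/50) = 0.2 SD. The largest value shown is 0.15/0.2 = 0.75 of a standard error. Equal switch rates remove the shift only if participants in both arms react in the same direction.

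**5. Dosing frequency.** Trial procedure sets once-daily night-time dosing without exception. Dose and medication modification gives eplerenone "at the same dose but twice a day". No frequency is stated for irbesartan, so reading it as still once nightly is an inference. On that reading, only eplerenone switchers leave the standard, and their time since last dose at clinic BP and ABPM may differ from that of other participants. The documents give no clock times for visits or for the second dose, so the difference cannot be computed.

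**The case against.** The strongest reply is that the unblinding rule is identical in both arms, touches only switchers, and keeps them in the analysis as intention to treat requires. All of that is correct. A reader might infer that the week-48 data of the two arms as a whole are gathered under different conditions. The documents do not support this: a difference between arms needs unequal switch rates or unequal reactions, and neither is given.

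A reader might also infer that BP assessment is unblinded. It is not shown to be. A blinded nurse takes readings with an automated device, and nothing lifts that blinding after a switch. The full protocol, which is not shown, may already tell participants not to disclose. What stands is a risk of disclosure.

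A third tempting inference is that an extra daytime dose biases BP in favour of the MRA arm. If one assumed a further 2 to 5 mmHg fall in 10% to 20% of that arm, the mean would move by 0.10 × 2 = 0.2 to 0.20 × 5 = 1.0 mmHg. The planned difference is 17.2 − 5.4 = 11.8 mmHg, and the standard error is 10 × √(2/50) = 2.0 mmHg. Those inputs are not in the documents, which also describe eplerenone as the less potent drug, so even the sign is open. In a pragmatic titration trial, part of any such effect may belong to the treatment strategy.

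It is also fair that the triggering complaint arises while the participant is blinded, that hyperkalemia is a laboratory outcome, that SF-36 is one of several secondary objectives, and that most readers would take the eplerenone instruction as a specific exception. These points limit the size of the concern. They do not explain why disclosure must be automatic or supply a blinded SF-36 value after the switch.

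**Conclusion.** The point holds in limited form. Automatic disclosure exposes the week-48 SF-36 and later symptom reports of switchers in either arm to reporting bias. The exposed group is selected by drug-specific side effects. The size is unknown because no switch rates are given. On assumed rates of 10% to 20% and an assumed reaction of 0.2 to 0.5 SD, the SF-36 difference moves by 0 to 0.15 SD, which is probably modest. For SF-36 the loss cannot be repaired afterwards.

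The two statements on dosing frequency are inconsistent as written and must be reconciled. Which regimen should apply is for the sponsor. Time since last dose may differ for eplerenone switchers, but no direction or size of BP effect follows from the documents.

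**What to change.** 1. Replace automatic unblinding with disclosure only where it is needed. Where feasible, supply the replacement drug through the existing third-party encapsulation. *Cost:* a small supply cost. A change in dosing frequency may still let some eplerenone switchers guess their arm.
2. Instruct any unblinded participant not to reveal the treatment to the BP nurse or the echocardiography technician. *Cost:* one line of protocol text and a reminder at visits.
3. Report SF-36 with unblinded switchers identified, and keep the intention-to-treat analysis as primary. An SF-36 taken at the switch visit is no substitute for the week-48 value. It would be collected at varying times, when side effects had prompted a change, and would not estimate week-48 quality of life. *Cost:* a flag in the database and one extra table.
4. Reconcile Trial procedure with Dose and medication modification on dosing frequency, and state the frequency for irbesartan. *Cost:* wording only.
5. Record time since last dose at each clinic BP reading and ABPM, so that any difference can be described. *Cost:* one additional data field.
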